## 6 STUDY DESIGN

### 6.1 Overall Study Design and Plan

#### 6.1.1 Study design

This is a phase 4 multicentre, open-label study of amyloid PET imaging of participants who have one of the following syndromic diagnoses: SCD-plus, MCI, or dementia where AD is in the differential diagnosis. Participants will be randomised to 3 arms. Arms 1 and 2 allow testing the impact of amyloid PET on diagnostic confidence, patient management, and ultimately decision making and the cost-effectiveness of dementia care. Arm 3 allows to investigate the optimal timing of amyloid PET imaging in the diagnostic workup.

The baseline visit must take place within 14 days after the screening visit and can be combined with the screening visit. At baseline, the investigator will record the syndromic diagnosis made by the managing physician, the managing physician's confidence in that diagnosis, and the managing physician's estimate of the likelihood that the patient's symptoms are due to AD. (According to [\[Johnson et al, 2013\]](#), the managing physician is a dementia expert trained and board-certified in neurology, psychiatry, or geriatric medicine who devotes a substantial proportion [at least 25%] of patient contact time to the evaluation and care of adult acquired cognitive impairment or dementia.). The investigator and the managing physician may be but do not have to be the same person. Participants will be stratified by syndromic diagnosis (SCD-plus, MCI, or dementia) and then randomly assigned (1:1:1) to 1 of 3 arms:

- **Early Amyloid PET Arm:** Participants will undergo amyloid PET imaging within 4 weeks after the baseline visit. Amyloid PET will be carried out with high priority over other diagnostic exams except MRI in the early amyloid PET arm. The results of the scan must be communicated to the managing physician as soon as available. Early Amyloid PET arm participants will undergo an optional second amyloid PET scan within at 12 to 18 months window after the initial scan.
- **Late Amyloid PET Arm:** Participants will undergo amyloid PET imaging at 8 months ( $\pm 8$  weeks) after baseline.
- **Free Choice Arm:** The managing physician will decide whether the participant undergoes amyloid PET imaging. The imaging can be done at any time within 12 months after baseline. The reason for the choice will be collected.

In all Arms, between Baseline visit and Week 12 visit, each time a biomarker is available, the result must be communicated to the managing physician, and the etiological diagnosis as well as the diagnostic confidence must be collected immediately. This will provide a sequential collection of diagnosis and diagnostic confidence up to Week 12 visit.

Amyloid load will be defined on the basis of visual reads at all time points. Only for the secondary aim of the disease modelling, amyloid load will be defined quantitatively. The results of the optional second amyloid PET scans (early amyloid PET arm) will be provided to the managing physician and may be used for clinical purposes.

The goal will be to enrol 100 participants per stratum in each arm, for a total of 900 participants.

Sites will be using PET-CT or PET-MR depending on what technology is available at each site.

Participation in the study will not prevent participants from having any currently available diagnostic investigation, but rather will give participants the opportunity to have access to amyloid PET imaging, a diagnostic test approved by the European Medicines Agency but not yet reimbursed by most national health services.

The study will comprise the following clinical visits and timepoints:

- A baseline clinical visit (Visit 0 [V0] at Time 0 [T0]), within 14 days after screening
- A timepoint 12 weeks after baseline (T1); no clinic visit is required at that time
- A clinical visit at 6 months  $\pm$ 14 days (V1 or T2), and
- An optional clinical visit at 13 months  $\pm$ 4 weeks (V2 or T3)

Amyloid PET imaging (conducted at the local sites and read visually) will not be considered a separate clinical visit.

At T1, the investigator will review the result communicated by the managing physician (if the investigator and the managing physician are not the same person) and record the etiologic diagnosis made by the managing physician, rate the managing physician's diagnostic confidence (0% to 100%, visual analogue scale [VAS]) as well as the managing physician's estimate of the likelihood that the patient's symptoms are due to AD (0% to 100%, VAS), and record the effective date of the managing physician's etiologic diagnosis and management plan. This does not need to be a clinical visit.

At the baseline visit, all participants will receive a diary/questionnaire to collect information on the use of medical resources. Patients with dementia will be asked to provide a contact name for a caregiver who will be contacted in order to fill a part of the medical resources questionnaire. The caregiver session is requested only for patients with dementia. If there is no caregiver, that part of the questionnaire will be left blank.

The study design is outlined in Figure 1.

[figure not shown]

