**Figure 1 Study Diagram**

### 6.1.2 Follow-up amyloid PET Image visit

Participants assigned to the Early Amyloid PET arm will have an optional second amyloid PET scan (performed 12 to 18 months after the initial scan) and an additional study visit (within 28 days after the optional second scan). The change in amyloid load between scans will be quantified.

AEs that occur within 48 hours of study drug administration and all SAEs occurring within 30 days of study drug administration will be recorded.

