### 8.3.2 Randomisation

This is a phase 4, open label, randomised study.

Patients will be randomised in a 1:1:1 ratio into 1 of the following 3 groups:

- **Early Amyloid PET arm:** These participants will undergo amyloid PET imaging within 4 weeks after baseline. The results of the PET imaging must be communicated to the managing physician as soon as they are available. Amyloid PET will be carried out with high priority for early amyloid PET arm patients. For participants in this arm, an optional second amyloid PET scan will be performed 12 to 18 months ( $\pm 28$  days) after the initial scan.
- **Late Amyloid PET arm:** These patients will undergo amyloid PET imaging at 8 months  $\pm 8$  weeks after baseline.
- **Free Choice arm:** The managing physician will choose whether and when each participant will have amyloid PET imaging at any time between baseline and 12 months after baseline.

Randomization will be performed by using permuted blocks assuring equal numbers to all arms. Randomization will be stratified by centre and baseline syndromic diagnosis. Participants will be randomly assigned (1:1:1) to 1 of 3 arms and randomization will continue until 300 SCD plus, 300 MCI, and 300 dementia where AD is a differential diagnosis have been included.

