## **9.6 Amyloid PET for Late Amyloid PET Arm, 8 Months ( $\pm$ 8 Weeks After Baseline)**

All female participants of childbearing potential must have a negative pregnancy test before the imaging study is done. The participants in the Late Amyloid PET arm of the study will undergo amyloid PET imaging at 8 months ( $\pm$ 8 weeks) after baseline. Amyloid PET scan must take place after the T2 visit at 6 months  $\pm$  14 days.

If the managing physician chooses to order amyloid PET imaging for the participants in the Free Choice arm, those participants may undergo the imaging at any time from baseline to 12 months after baseline.

The following will be recorded for all participants who have undergone amyloid PET imaging:

- Review of current medications
- Amyloid PET scan results
- All AEs that occurred within 48 hours of study drug administration
- All SAEs occurring within 30 days of study drug administration

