#### 10.1.2 Secondary endpoints

The timepoints are defined as follows:

- T0 = baseline,
- T1 = 12 weeks after T0,
- T2 = 6 months ( $\pm 14$  days) after T0,
- T3 = 13 months ( $\pm 4$  weeks) after T0;
- T4 =  $\leq 28$  days after the optional second scan, which will be 12 to 18 months after T0.

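### The Early arm's optional second scan has inconsistent timing and no set order against T3, so three T3 Early-vs-Late comparisons can mix PET timing with number of PETs

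*Protocol*

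**What the plan says.** **First Early scan.** Section 6.1.1: "Participants will undergo amyloid PET imaging within 4 weeks after the baseline visit".

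**Second Early scan.** It is optional and is timed in three ways:
- Sections 6.1.1, 6.1.2 and 9.9 count from the first scan with no tolerance. Section 6.1.2 has an "optional second amyloid PET scan (performed 12 to 18 months after the initial scan".
- Section 8.3.2 ("an optional second amyloid PET scan will be performed 12 to 18 months"), section 9.1 and the Synopsis under Treatment of Participants also count from the first scan, but add ±28 days.
- Section 10.1.2 and the Synopsis under Secondary Endpoints count from baseline. T4 is set "after the optional second scan, which will be 12 to 18 months after T0".

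**Disclosure.** Section 6.1.1 says the "results of the optional second amyloid PET scans (early amyloid PET arm) will be provided to the managing physician" and allows clinical use of them.

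**T3.** This visit is optional, at 13 months after baseline. The window is ±4 weeks in sections 6.1.1, 9.7 and 10.1.2, and ±14 days in Table 1.

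**Late arm.** One scan is planned, at 8 months ±8 weeks. Section 9.6 adds an order: "Amyloid PET scan must take place after the T2 visit at 6 months" (±14 days). No such sentence links the second Early scan to T3.

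**What is compared at T3.** Sections 10.1.2.1 and 10.1.2.2 name confidence, AD likelihood and change in management plan as Early-vs-Late endpoints that include T3. Resource use is compared between arms (10.1.2.3) and is collected at T3 among other times (10.3.14).

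**The concern.** The Early-vs-Late contrast is meant to show what difference the timing of amyloid PET makes. By T3 a Late participant scanned on schedule has one study scan. An Early participant may have two, and the physician who gives the T3 ratings may have seen the second result only days before. Section 5.4.2.4 gives the repeat imaging a different purpose, the stability of amyloid load, so its influence on the T3 ratings is a by-product.

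The extra information reaches one arm only, and within it only those who agreed to a further scan under a separate consent. A T3 difference in confidence or management could then not be put down to timing alone. The second scan would also count as resource use in one arm.

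Section 12.5.3 does not help: it censors or excludes for dropout and major protocol deviation, and an on-schedule second scan is neither. If the order of disclosure and rating is not captured when the data are collected, it may not be recoverable at analysis.

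**Working it through.** The protocol gives no figure for this overlap, so there is none to reproduce. The check compares date windows, with 1 month = 365.25/12 = 30.44 days and baseline as day 0.

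**Inputs**
- First Early scan: day 0 to 28 (6.1.1).
- Second scan: 12 to 18 months later, that is 365 to 548 days, with or without ±28 days (6.1.2; 8.3.2), counted from the first scan or from T0 (10.1.2).
- T3: 13 × 30.44 = day 396, ±28 days (10.1.2) or ±14 days (Table 1).
- Late scan: 8 months ±56 days (9.6).

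**Step 1: windows**
- T3 by the text: 396 ± 28 = day 368 to 424. By Table 1: 396 ± 14 = day 382 to 410.
- Late scan: 243.5 ± 56 = about day 188 to 300, always before T3.

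| Reading of the second scan | Earliest day | Before nominal T3 | Before latest T3 (±4 weeks) |
|---|---|---|---|
| From first scan, no tolerance | 365 (first scan day 0) to 393 (day 28) | 30 to 2 days | 58 to 30 days |
| From first scan, ±28 days | 337 to 365 | 58 to 30 days | 86 to 58 days |
| From T0 | 365 | 30 days | 58 days |

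With Table 1's T3 window, the latest T3 is day 410. The least favourable case still leaves 410 − 393 ≈ 16 days before rounding. The windows overlap under every reading.

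**Step 2: what is out of reach.** The earliest possible second scan is day 337, about 11 months. T1 is at 12 weeks and T2 at 6 months ±14 days, so neither can be affected.

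**Step 3: illustrative share.** Assume uniform timing in every window. The group is Early participants who have both the second scan and the T3 visit.
- *From first scan, ±28 days.* The mean earliest second scan is 14 + 365.25 − 28 = 351.25. The mean T3 is 395.7. The width is 182.6 + 56 = 238.6. Share = (395.7 − 351.25)/238.6 = 18.6%. This is exact, because every T3 falls after every earliest scan date.
- *From first scan, no tolerance.* The same formula gives (395.7 − 379.25)/182.6 = 9.0%. Some T3 visits now fall before the scan window opens and count as zero rather than negative, which raises the share. Simulation gives 9.2% (T3 ±14 days) to 10.0% (T3 ±28 days).
- *From T0, no tolerance.* (395.7 − 365.25)/182.6 = 16.7%.

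**Step 4: scan date is not disclosure date.** The protocol gives no time from scan to report. With an assumed 14-day lag, the no-tolerance share falls to about 3-5% and the ±28-day share to about 13% (both from the first scan).

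**The case against.** The strongest points on the other side, and what stands of each:

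- **Few comparisons are touched.** This stands. A reader might infer that every T3 outcome is an Early-vs-Late endpoint. Sections 10.1.2.1 and 10.1.2.3 list etiologic diagnosis and patient-related outcomes within each arm. Section 12.6.1 permits between-arm tests at T3 in general terms but does not redefine them. Resource use matters only so far as T3 data enter it. Workup cost stops at the high-confidence diagnosis, so a later scan is outside it for anyone who reached 90% earlier.
- **The share is small and uncertain.** This largely stands. Both the scan and the visit are optional. The effect on the arm as a whole is the share above multiplied by second-scan uptake among T3 attenders, which the protocol does not give. Higher shares, around 28-39%, follow only if sites book the second scan at 12 to 14 months, and no such pattern is stated.
- **The schedule implies an order.** Table 1 puts the second-scan and T4 columns after T3, but column order is not a rule, and the stated windows permit the reverse. The study diagram is not available to this review and might show a sequence.
- **The second scan is part of the Early strategy.** This stands in part. As a comparison of assigned strategies, the T3 contrast remains a valid randomised one. It then answers a wider question than timing alone.
- **Removing affected ratings would do harm.** This stands. Dropping T3 ratings made after disclosure conditions on a post-randomisation event that exists in one arm only, and would break the randomised comparison to cure a limited contamination.

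**Conclusion.** The point holds for the T3 secondary comparisons of confidence, AD likelihood and management plan, and for resource use so far as T3 data enter it. The second scan can precede T3 under every stated window, its result goes to the rating physician, and no text orders the two, although section 9.6 does so for the Late scan and T2.

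The size can only be illustrated. Assuming uniform timing from the first scan, about 9-10% of those with both optional events are scanned before T3 without the tolerance, and about 19% with it. Any lag to disclosure lowers these figures. They are proportions exposed, not effects on the endpoints, and the proportion of the whole Early arm is smaller and cannot be derived from the protocol.

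A reader might infer that the main result is at risk. It is not: the primary endpoint is at T1, and the second scan cannot occur before about 11 months. Nor do the documents show that the T3 comparisons are invalid. They show that a one-arm influence is possible and, as written, would go unmarked.

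**What to change.** 1. **Reconcile the windows.** Give the second scan one origin (first scan or T0) and one tolerance (with or without ±28 days) in the Synopsis, 6.1.1, 6.1.2, 8.3.2, 9.1, 9.9, 10.1.2 and the Table 1 notes. Give T3 one window in the text and Table 1. Which values are right is for the sponsor to decide.
2. **Fix the order of data entry.** Where the second-scan result is still pending at T3, state that the T3 ratings and questionnaires go into the eCRF before it is reviewed. This governs data entry only and should not delay any result needed for care. Diagnosis and plan after the second scan are already recorded at T4 (9.9).
3. **Record the order.** For each T3 rating, capture whether it was made before or after second-scan disclosure.
4. **Analysis.** Keep all randomised participants in the main T3 contrast, whatever the order. Add a sensitivity analysis for ratings made after disclosure. Report resource use with and without the second research scan.

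Cost: one date or flag field, one sensitivity analysis and some wording. No visit or scan is added.

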## 9.8 Study Completion

Visit 2 must be completed within 13 months ( $\pm 4$  weeks) of the baseline visit. Participants who do not complete visit 2 within this period will not be replaced.

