### **10.3.16 Etiologic diagnosis**

The etiologic diagnosis made by the managing physician at T1, T2, and T3 will be recorded in the eCRF. Earlier on in the workup, when diagnostic hypotheses are made, up to 4 diagnostic hypotheses will be recorded.

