### **12.5.3 Handling of missing values/censoring/discontinuations**

The reasons for incomplete data are many and include major protocol deviations, dropout because of study withdrawal or death, non-attendance at clinical visits, missing questionnaire items, uninterpretable images, etc.

The primary efficacy analysis will be conducted on the PPS population, which is based on complete cases.

Secondary efficacy analyses will be conducted on the FAS population. In time-to-event analyses, dropout and major protocol deviations are accounted for by censoring at the time of dropout or protocol deviation. In cross-sectional analyses and analyses of change between 2 timepoints, only complete cases will be included. Cases with a major protocol deviation before the first timepoint in the cross-sectional or change analysis will be excluded. The longitudinal mixed-effect analyses will be based on the observed cases. Data will be censored after a major protocol deviation. The underlying assumption in all analyses is that missing data are missing at random and not related to the primary outcome.

The proportion of missing data at each time point will be computed for the Early Amyloid PET, Late Amyloid PET, and Free Choice arms separately, and stratified for SCD Plus, MCI, and dementia.

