## **12.6 Secondary Analyses**

### **12.6.1 Secondary efficacy variables**

In the analyses of the secondary efficacy variables, a cross-sectional difference between arms in a secondary endpoint at T1, T2, T3, or T4 (see Table 1) will be carried out by a chi-squared test if the endpoint is dichotomous, a 2-sided *t*-test if the endpoint is normal, and Mann-Whitney test if the endpoint is categorical or continuous and non-normal. The effect of baseline characteristics such as age, gender, MMSE, etc will be studied by a linear or logistic regression model.

A difference between study arms in the longitudinal change of a secondary endpoint will be tested by means of logistic or linear regression where the first measurement is a covariate (ANCOVA analysis) and the second measurement is the outcome. Differences in longitudinal

trends between arms will also be examined by means of the mixed-effects regression model. The effects of baseline characteristics such as age, gender, MMSE, etc. will be studied by including them in the regression models.

All tests will be 2-sided and the significance level will be set at 5%. Bonferroni corrections for multiple testing will be applied when appropriate. Point estimates will be presented together with 95% Wald confidence intervals. A 95% non-parametric confidence interval will be constructed if the estimate is non-normal.

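### The 13-month endpoints, including the Late arm's only scheduled post-scan record of diagnosis and management, rest on an optional visit and may be read from selected attenders

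*Protocol*

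**What the plan says.** **Status and window of the visit.** Section 6.1.1 lists "An optional clinical visit at 13 months". The synopsis, Table 1 and Section 9.7 also call it optional. Section 9.8 reads "Visit 2 must be completed within 13 months". The window is ±4 weeks in Sections 6.1.1, 9.7, 9.8 and 10.1.2, and ±14 days in Table 1.

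**Endpoints that use T3.** Section 10.1.2 names T3 for etiologic diagnosis (in each arm), diagnostic confidence and likelihood of AD (Early versus Late), management-plan changes (Early versus Late) and patient-related outcomes (in each arm). Section 9.7 records these items at the T3 clinic visit.

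**Late-arm scan.** It is due at 8 months ±8 weeks, and Section 9.6 adds: "Amyloid PET scan must take place after the T2 visit".

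**Analysis.** Section 12.5.3: "In cross-sectional analyses and analyses of change between 2 timepoints, only complete cases will be included". Section 12.8 rules out imputation. Section 12.5.3 also plans mixed-effects models on observed cases, assumes missingness at random throughout, and reports missingness at each timepoint by arm and stratum. For change between two timepoints, Section 12.6.1 uses regression "where the first measurement is a covariate (ANCOVA analysis) and the second measurement is the outcome".

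**T1 as a contrast.** At T1 the physician's ratings are recorded although "no clinic visit is required at that time" (Section 6.1.1).

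**The concern.** If attendance at T3 is a choice, the people seen there need not represent those randomised. If attendance also depends on outcome differently in the two arms, a complete-case contrast at T3 mixes the effect of scan timing with the effect of who came back. In an open-label trial, where the arms receive their scan results months apart, that is a plausible worry.

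The Late arm is the more exposed. If T3 is missed, nothing scheduled shows what its scan did to diagnosis or management, and a later analysis plan cannot recover ratings that were never collected.

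The ANCOVA rule raises a second question. When the first of the two timepoints is T1 or T2, the covariate was measured after randomisation, and T1 is where early PET is hypothesised to act. Adjusting for it can remove part of the difference between arms.

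**Working it through.** **1. Is T3 the Late arm's only scheduled post-scan record of these outcomes?** With months of 30.4375 days:

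| Event | Days after baseline |
|---|---|
| T2, 6 months ±14 days | 182.6 ± 14 = 169 to 197 |
| Late scan, 8 months ±8 weeks | 243.5 ± 56 = 188 to 300 |
| T3, 13 months ±4 weeks | 395.7 ± 28 = 368 to 424 |
| T3 with Table 1's ±14 days | 395.7 ± 14 = 382 to 410 |

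The T2 and Late-scan windows overlap slightly, but Section 9.6 places the scan after T2, so T2 is never post-scan in this arm. Could another record fill the gap?
- Section 9.6 records medications, scan result, AEs and SAEs with the scan, but no diagnosis, confidence or plan.
- Recording triggered by a new biomarker result stops at Week 12 (Sections 6.1.1 and 9.4).
- Section 10.3.16: "The etiologic diagnosis made by the managing physician at T1, T2, and T3 will be recorded in the eCRF".
- T4 is for the Early arm only (Table 1, note a; Section 9.9).

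No other scheduled record remains.

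**2. The plan's own figures.** Section 12.7 concerns 12 weeks with 10% loss: 270 per arm, 90 per arm in each stratum. Base rates are not stated; I assumed proportions centred on 50%. With a continuity correction,

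power = Φ{[d − 1/n − z·√(2p̄(1−p̄)/n)] / √[(p₁q₁ + p₂q₂)/n]}.

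For d = 0.15, n = 270: (0.1463 − 1.96 × 0.0430)/0.0425 = 1.46, power 92.7% (stated 93%). Differences of 20 and 10 points give 99.6% and 61.0% (stated 99.6% and 61%). A stratum at 25 points with α = 0.05/3 gives 79.9% (stated 80%). The figures reproduce. None is given for T3.

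**3. Loss of precision at T3.** Same formula, binary outcome, attendance assumed equal in both arms:

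| Attendance | n per arm | Power, 15 points | Power, 10 points |
|---|---|---|---|
| 90% | 270 | 93% | 61% |
| 70% | 210 | 85% | 50% |
| 60% | 180 | 79% | 43% |
| 40% | 120 | 59% | 29% |

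**4. Possible bias at T3.** Assume the true proportion is 60% in both arms. If attendance is a with the outcome and b without it, the proportion among attenders is 0.6a/(0.6a + 0.4b).

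| Early a/b | Late a/b | Early seen | Late seen | Apparent difference |
|---|---|---|---|---|
| 70/70% | 70/70% | 60.0% | 60.0% | 0 |
| 60/80% | 60/80% | 52.9% | 52.9% | 0 |
| 60/80% | 70/70% | 52.9% | 60.0% | −7.1 points |
| 50/80% | 70/70% | 48.4% | 60.0% | −11.6 points |
| 50/80% | 80/50% | 48.4% | 70.6% | −22.2 points |

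With 300 randomised per arm, the third and fourth rows give false-positive rates of about 30% and 64%. All attendance figures are assumptions; reversing the patterns reverses the sign.

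**5. The post-randomisation covariate.** In a linear model,

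adjusted T2 contrast = T2 difference − slope × T1 difference.

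Assume a T2 difference of 10 points in confidence:
- slope 0.5, T1 difference 20: 10 − 0.5 × 20 = 0
- slope 0.5, T1 difference 10: 10 − 0.5 × 10 = 5
- slope 0.25, T1 difference 20: 10 − 0.25 × 20 = 5
- T1 difference 0: nothing is removed

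Confidence, likelihood of AD and patient outcomes have a T0 value. The management plan does not (Table 1; Section 10.3.17 lists T1, T2 and T3), so any pairwise covariate for it is post-randomisation.

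**The case against.** Much of the opposing case stands, and it limits the point.

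- A reader might infer that the T3 contrasts have lost the randomised comparison, or that attenders select themselves. The protocol gives no attendance rate and does not say who decides on attendance. Differential attendance is assumed, not shown.
- A reader might size the bias as the gap between attenders and non-attenders times the difference in attendance between arms. That needs the same gap in both arms. In the third row of the bias table, overall attendance is 68% versus 70% and the Early gap is about 22 points (52.9% versus 75.0%). The product is about 0.4 points, whereas the actual bias is 7.1.
- A reader might expect the Late arm to attend more because its scan is more recent. But the Early arm is offered a second scan at 12 to 18 months after its first, which overlaps T3 and gives it a reason to return. The direction is unknown.
- Not every T3 analysis is complete-case. Mixed models on observed cases are planned, and missingness by arm will be visible. Those models still assume missingness at random, and in them the Late arm's post-scan information comes only from T3 attenders.
- The ANCOVA rule does not name T1 or T2 as the covariate. Diagnosis and patient outcomes are listed within each arm, and an adjusted contrast of exactly zero comes from chosen inputs. But confidence and likelihood of AD are Early-versus-Late endpoints across T0 to T3, and the management plan across T1 to T3, so the rule as written reaches such pairs.
- Section 9.8 can be read as a window rule, since it goes on to say that participants who miss Visit 2 are not replaced. The two windows still conflict.

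**Conclusion.** The point holds in this limited form. T3 endpoints rest on a visit whose status and window are stated inconsistently. For the Late arm it is the only scheduled post-scan record of diagnosis, confidence, likelihood of AD, management plan and patient outcomes; it is not the only post-scan record of any kind. Complete-case analyses at T3 may therefore compare selected attenders.

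The protocol does not determine the size or direction of any bias. With no true difference it is zero if attendance is unrelated to outcome or related to it identically in both arms. The other assumed patterns gave about 7 to 22 points. The effect of a T1 or T2 covariate likewise depends on assumed values.

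Only secondary endpoints are affected; the primary endpoint is at 12 weeks and does not use T3. The change is still worth making, because missing ratings cannot be recovered later and the remedy is cheap.

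**What to change.** 1. **Collect the physician-rated items from everyone.** At 13 months, record etiologic diagnosis, confidence, likelihood of AD and management plan for every participant without requiring a clinic visit, as at T1. Report the patient questionnaires as limited to attenders; this change does not cure selection there. Cost: amendment wording and physician and eCRF time. Some ratings may be made without seeing the patient and may repeat an older opinion, so record whether a visit took place.
2. **Change the covariate rule in Section 12.6.1.** For Early-versus-Late contrasts, use T0 as covariate where it exists (confidence, likelihood of AD, patient outcomes). For the management plan, compare the randomised arms with no T1 or T2 covariate. Make the already planned mixed model on all observed data the main analysis of change for outcomes with repeated measures. Cost: wording only.
3. **Reconcile the text.** Sections 6.1.1, 9.7 and 9.8, the synopsis and Table 1 should give one status and one window for the 13-month visit, so that sites know whether a missed or late visit is a deviation. Cost: wording only.
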